#### 2.6.2. Effectiveness Outcomes

The primary effectiveness outcome is the CSS score at Week 6. The CSS is a scale for the subjective assessment of cough severity and frequency that is reported by the patient during the daytime (08:00–20:00) and nighttime (20:00–08:00), and each subdomain of the scale is assigned 6 points, from 0 to 5. The total score is calculated as the sum of the daytime and nighttime scores (0–10 points) [19]. The validity and replicability of the Korean version of CSS have been verified [20]. Until Week 9, participants will be instructed to self-evaluate the CSS twice a day and record the score in a cough diary. During the telephonic follow-up survey (Week 24), participants will be asked to respond on their cough symptoms during the daytime and nighttime of the previous day. For statistical analysis, the average value (total, daytime, and nighttime scores) of the CSS since the previous visit that has been recorded in the cough diary and will be collected at each visit (excluding the baseline visit) will be used, and the average value of the previous 7 days will be used for determining the status at the baseline visit. The investigator will educate the participants on how to write a cough diary at every visit and attempt to minimize omissions in records. If less than 70% of the cough diary distributed at each visit has been completed, the participant will be dropped out.

The secondary outcome measures include the CSS (at weeks 3, 9, and 24), cough visual analog scale (VAS), the Leicester Cough Questionnaire (LCQ), the Hull Airway Reflux Questionnaire (HARQ), Integrative Medicine Outcome Scale (IMOS), Integrative Medicine Patient Satisfaction Scale (IMPSS), a five-level version of the EuroQol Five-dimensional Descriptive System (EQ-5D-5L), the EuroQol visual analog scale (EQ-VAS), yin deficiency score, and serum biomarkers.

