### 2.8. Statistical Analysis

The statistical analysis of this clinical trial, in principle, will use full analysis set (FAS) analysis as the main analytical method; if necessary, a per protocol set (PPS) analysis will be additionally conducted. The FAS analysis group is defined as comprising participants with data measured for the outcome measures at least once after being randomly allocated, and all data obtained therefrom are included in the analysis. The PPS analysis comprises only participants included in the FAS analysis who have completed the entire process as specified in the protocol and have no significant violations that affect the trial results. The safety analysis includes all the data obtained from the participants who received the investigational product at least once. 

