All statistical analysis is based on a two-sided test, and the significance level is set at 0.05. For continuous data, the mean and confidence interval are presented, whereas for categorical data, the frequency and percentage are presented. Statistics on the demographic and socioeconomic characteristics are presented for each group. Depending on normality, continuous data are analyzed using the independent *t*-test or Wilcoxon rank sum test, whereas categorical data are analyzed using the chi-square or Fisher’s exact test. For analyzing the effectiveness outcomes, the mixed-effect model repeated-measures method will be used, with each group and visit as the fixed factor and the participants as the random factor. If necessary, variables that show statistical differences in demographics or variables that can affect chronic cough will be set as fixed factors and analyzed. Intragroup differences in values before and after treatment will be analyzed, based on normality, with the Student’s paired *t*-test or Wilcoxon signed rank test. The IMOS and IMPSS scores are analyzed using Fisher’s exact test. The repeated-measures analysis of variance method is used to compare the difference in trend change between groups for the effectiveness outcomes, and Dunnett’s procedure is used for correction of the multiple-comparison analysis. If necessary, subgroup analysis will be performed by categorizing the participants according to their baseline characteristics (chronic cough pattern identification [29], presence of yin deficiency [27], sex, age, etc.). For the analysis of safety outcomes, the chi-square or Fisher’s exact test will be performed to compare the number of adverse events in the study groups. In addition, AST, ALT, BUN, creatinine, and vital signs will be analyzed using a paired *t*-test or Wilcoxon signed rank test to determine differences from before to after treatment. No interim analysis has been planned. All statistical analyses will be performed by a statistician, independently of trial procedure, by using the statistical program SAS^®^ Version 9.4 (SAS Institute Inc., Cary, NC, USA). 

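### For CSS, the stated random-participant model and repeated-measures ANOVA assume equal variance of all visit differences, but the protocol's scoring windows (7 days, about 21 days, one recalled day) break that assumption

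*Protocol article*

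**What the plan says.** Section 2.8 gives the mixed-effect repeated-measures model for the effectiveness outcomes "with each group and visit as the fixed factor and the participants as the random factor". It names no residual covariance structure and no group-by-visit term. A second method is then added: "The repeated-measures analysis of variance method is used to compare the difference in trend change between groups for the effectiveness outcomes". Multiplicity is to be handled by Dunnett's method. No sphericity correction is mentioned. The test level is fixed: "All statistical analysis is based on a two-sided test, and the significance level is set at 0.05".

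Section 2.6.2 makes CSS at Week 6 the primary effectiveness outcome and CSS at Weeks 3, 9 and 24 secondary. It also fixes how each value is formed:

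- **Baseline:** "the average value of the previous 7 days will be used for determining the status at the baseline visit".
- **Weeks 3, 6 and 9:** "the average value (total, daytime, and nighttime scores) of the CSS since the previous visit", which is about 21 days because visits are 3 weeks apart.
- **Week 24:** by telephone, "participants will be asked to respond on their cough symptoms during the daytime and nighttime of the previous day", so a single day.

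Table 1 places Week 24 fifteen weeks after Week 9, while the earlier visits are three weeks apart.

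**The concern.** A participant effect as the only random term implies compound symmetry: the same variance at every visit and the same correlation between any two visits. Univariate repeated-measures ANOVA needs the slightly weaker condition that every difference between two visits has the same variance. In both cases a single within-person error, pooled over visits, serves every comparison of change.

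A mean of 21 diary days varies less from one period to the next than a mean of 7 days, and much less than one day. Pooling them gives Week 24 an error that is too small and Week 6 an error that is too large. A chance Week 24 group difference then becomes easier to declare, and a real difference in change at Week 6, the primary time point, becomes harder to detect. With 12 to 15 people per arm there is little room for either.

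**Working it through.** **Inputs from the protocol.** Windows of 7, 21, 21, 21 and 1 days (section 2.6.2); two-sided 5% level (section 2.8); 12 evaluable and 15 randomised per arm (section 2.7). The one related figure that can be reproduced is the target size: 24 / (1 - 0.20) = 30, or 15 per arm, as stated. The plan gives no power, SD, day-to-day variance or correlation, so all variances below are assumptions.

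**Step 1: closed form, independent daily scores.** Let the daily within-person variance be 1. The visit variances around the person's own level are 1/7, 1/21, 1/21, 1/21 and 1.

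- Pooled within-person variance: (1/7 + 3/21 + 1)/5 = 0.257.
- Variance assigned to every change from baseline: 2 × 0.257 = 0.514.
- True variance of the Week 24 change: 1/7 + 1 = 1.143. The standard error is too small by a factor of √(1.143/0.514) = 1.49.
- True variance of the Week 6 change: 1/7 + 1/21 = 0.190. The standard error is too large by a factor of √(0.514/0.190) = 1.64.

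The daily variance cancels from both ratios, so under independent days they do not depend on the SD.

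**Step 2: simulation under no group difference** (complete, balanced, normal data; 20,000 or more trials per scenario). The change columns test the group difference in change from baseline with the pooled error.

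| Scenario | Week 24 change | Week 6 change | Uncorrected trend F |
|---|---|---|---|
| Control: equal windows at all visits | about 5% | about 5% | about 5% |
| Protocol windows, independent days | about 19% | about 0.2% | about 10-11% |
| Added autocorrelation, visit-level variance or slow drift | 5.6-17% | 0.5-4.8% | 5.0-9.1% |

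The control shows that the unequal windows cause the distortion in the second row. Two examples from the third row, both with 15 per arm: a daily autocorrelation of 0.9 gives 8.9% at Week 24 and 4.8% at Week 6. A visit-level variance equal to the between-person variance, with a daily variance one quarter of it, gives 5.6% and 4.6%.

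**Step 3: group difference in level instead of change.** With independent days, as the daily variance goes from 0.25 to 4 times the between-person variance, size goes from 7% to 20% at Week 24 and from 4.6% to 1.1% at Week 6. With correlation, visit-level variance or drift added, it is 5.9-12% at Week 24 and 3.1-4.8% at Week 6. The overall group effect averaged over visits keeps about 5% throughout.

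**Step 4: what repairs it.** Using each visit's own variance gives 4.7-5.2% at Week 6 and 4.7-5.4% at Week 24. A Greenhouse-Geisser correction brings the trend F to 4.0-5.4%, but it does not touch visit contrasts that use the pooled error.

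**Step 5: is it enough to drop Week 24?** With windows 7, 21, 21 and 21, the pooled variance is (1/7 + 3/21)/4 = 0.0714, so 0.143 is assigned to a change whose true variance is 0.190. The standard error is now too small by √(0.190/0.143) = 1.15, and the Week 6 change test has a size of about 9% with independent days. The 7-day baseline still differs from the 21-day means, so removing Week 24 alone turns a strict test into a liberal one.

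**The case against.** The strongest reply is that the article leaves details open. It excludes neither an unstructured residual covariance nor an epsilon correction, and a condensed article may leave both to an analysis plan that is not shown. This limits the point to the text as written. It does not remove it, because section 2.8 does commit to a participant random factor and to a separate repeated-measures ANOVA, while section 2.6.2 commits to windows that do not fit them.

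Second, the largest figures do not belong to the quoted trend test. That test is an omnibus comparison with a size of at most about 11%, and a standard correction repairs it. The 19% and 0.2% belong to visit-specific changes from baseline. The mixed model lists no group-by-visit term, and read literally it tests one overall group effect, which is sound. This stands, with one qualification: such a model gives no group comparison specific to Week 6, which is the primary effectiveness time point.

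Third, a reader might infer that Week 24 is tested far too liberally and that the primary comparison is badly underpowered. The documents do not support that. They give no variances, and under strong autocorrelation or large visit-level variance Week 24 is close to nominal. The primary outcome is stated as the Week 6 score, a level, for which the loss is smaller. The trial's primary purpose is feasibility, and no power is claimed.

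Fourth, a reader might see a contradiction with the full-analysis-set rule that "all data obtained therefrom are included in the analysis", because classical repeated-measures ANOVA can delete anyone with a missed visit. That assumes an implementation the text does not specify. The same holds for a claim that a later trial would be sized on these standard errors: no passage says so.

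Finally, the window problem concerns CSS only. Cough VAS is defined with a 3-week recall, and LCQ and HARQ are not collected at Week 24.

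**Conclusion.** The concern holds in a limited form. For CSS, the analysis as written assumes equal variances of visit differences, and the protocol's own windows make that assumption implausible. The direction was the same in every scenario with the protocol's five windows: Week 24 liberal, Week 6 conservative, though the Week 6 effect was sometimes negligible. For change from baseline, size is about 6-19% at Week 24 and about 0.2-5% at Week 6, and the uncorrected trend F is at about 5-11%. The outer values for the change tests need independent daily scores.

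These figures rest on assumed variances, on complete normal data, and on reading section 2.8 without a visit-specific covariance or a sphericity correction. Performance with the expected 20% dropout was not tested. The point is worth correcting before analysis. It does not undermine the feasibility aims.

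**What to change.** In section 2.8, for CSS:

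1. Fit one mixed model with group, visit and group-by-visit as fixed effects and a within-participant covariance that lets variances differ by visit. Use unstructured, with heterogeneous Toeplitz as the stated fallback, and Kenward-Roger degrees of freedom.
2. Take the trend comparison and each visit contrast, including Week 6, from that model, and delete the separate repeated-measures ANOVA.
3. Analyse the one-day Week 24 telephone CSS separately. Do this in addition to step 1, not in place of it, for the reason shown in the last step of the working.

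The cost is a sentence or two of text and a change of covariance statement in the SAS code, with no new data. The small downside is more covariance parameters at n = 30. With baseline and Weeks 3, 6 and 9 in the model, an unstructured matrix has 4 × 5 / 2 = 10 parameters, against two for a participant effect plus one residual. Heterogeneous Toeplitz has 4 + 3 = 7. Leaving Week 24 out keeps this manageable, since five time points would need 5 × 6 / 2 = 15.

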For the cough VAS assessment, participants will self-evaluate their subjective discomfort based on cough severity, frequency, and urge to cough on a scale of 0 (no discomfort from coughing) to 100 (the highest discomfort imaginable) for the past 3 weeks [21]. This assessment will be undertaken at every visit, except for the screening visit, as well as during the telephonic follow-up survey (at Week 24), and will be investigated through a numerical rating scale (NRS) score from 0 to 100. The LCQ is a 19-item questionnaire designed to measure the quality of life of patients with cough and is divided into physical, mental, and social categories [22]. Each item is checked on a scale of 1 to 7, with higher scores indicating better health. The Korean version of the LCQ has been verified for validity and reliability [23]. The HARQ is a self-report questionnaire that measures cough hypersensitivity, and each of 14 questions is evaluated on a scale of 0 to 5. For normal individuals, the average score is 4 points, and the upper limit of the normal range is 13 points [24]. The IMOS is a tool for the investigator or participant to evaluate the degree of posttreatment improvement [25], and has been set as the investigator’s evaluation tool in this clinical trial. The IMPSS is an evaluation tool for ascertaining the participant’s treatment satisfaction [25]. Each tool is evaluated on a scale of 1–5 points. The EQ-5D-5L is a self-report questionnaire that is used to evaluate the quality of life, based on a 5-point scale over five areas: mobility, self-care, usual activities, pain/discomfort, and anxiety/depression [26]. The EQ-VAS asks participants to rate their own health from 0 (the worst imaginable health status) to 100 (the best imaginable health status) [26]. In case of telephonic follow-up (at Week 24), the EQ-VAS will be investigated through a 0 to 100 NRS. The Yin Deficiency Questionnaire is a pattern identification questionnaire with 27 questions, and the reliability and validity of this questionnaire have been established. Each question is evaluated on a 7-point Likert scale, of which points 1–4 are converted to 0 points and points 5–7 are converted to 1 point for calculation. The cutoff score for a yin deficiency diagnosis is 10 points [27]. The serum biomarkers include eosinophils, total immunoglobulin E (IgE), and plasma fibrinogen, which will be evaluated at the screening visit and at Week 6. In particular, during the telephonic follow-up survey (at Week 24), CSS, cough VAS, EQ-5D-5L/EQ-VAS, and cost questionnaires will be surveyed through a phone call.

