
#### 2.6.3. Safety Outcomes

To evaluate safety both before and after the administration of the investigational drugs, liver function (AST and ALT) and kidney function (blood urea nitrogen [BUN] and creatinine) tests will be conducted at the screening visit and at Week 6. In addition, the occurrence and frequency of adverse events will be evaluated at each visit through physical examination conducted by the investigator and through the participant’s self-report; moreover, the vital signs (blood pressure, pulse rate, and body temperature) will be measured at each visit and will be used as safety outcomes.

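### Section 2.8 uses an unordered test for the ordered IMOS and IMPSS ratings, and its adverse-event test is worded to count events, not participants

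*Protocol article*

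**What the plan says.** Protocol article, section 2.8, on the two global ratings: "The IMOS and IMPSS scores are analyzed using Fisher’s exact test". Section 2.6.2 describes IMOS as the investigator's rating of how much the participant has improved and IMPSS as the participant's satisfaction with treatment, and adds: "Each tool is evaluated on a scale of 1–5 points". Table 1 schedules both at weeks 3, 6 and 9.

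On safety, section 2.8 says that a chi-square or Fisher's "exact test will be performed to compare the number of adverse events in the study groups". Section 2.6.3 says that "the occurrence and frequency of adverse events will be evaluated at each visit", and Table 1 places the adverse-event inquiry at Visits 2 to 5. The safety population is broad: "The safety analysis includes all the data obtained from the participants who received the investigational product at least once".

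The error level for all of this is set once: "All statistical analysis is based on a two-sided test, and the significance level is set at 0.05". Section 2.8 already names the Wilcoxon rank-sum test for continuous data that are not normal, but does not use it for IMOS or IMPSS.

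**The concern.** **IMOS and IMPSS.** Both are ordered. Fisher's exact test on the five categories treats them as unordered labels, so rearranging the categories leaves the p-value unchanged. A consistent drift towards better ratings in one arm earns no more credit than a patternless difference of equal probability. The test also gives neither direction nor size of effect, which an exploratory trial of preliminary effect is meant to supply for the next study.

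**Adverse events.** Chi-square and Fisher's tests need independent units and a defined denominator. Events are collected by frequency over several visits, so one participant can contribute more than one. If events are the unit of the test, repeat events from one participant are counted as independent observations. This is the only between-group test that section 2.8 names specifically for safety outcomes; laboratory values and vital signs are given before-to-after paired tests.

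**Working it through.** **Inputs from the documents.** Two-sided 0.05 (section 2.8). 1:1 allocation (section 2.4). 12 per group needed and 15 per group targeted (section 2.7). IMOS and IMPSS scored 1 to 5 (section 2.6.2). The plan's sample size reproduces: 24 / (1 − 0.20) = 30. The documents state no power or error rate for either test at issue, and no rating distribution, effect size or adverse-event rate. Everything below that needs one of these is an assumption, shown over a range.

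**IMOS and IMPSS: power by simulation.** Fisher's exact test on the 2×5 table was compared with the Wilcoxon rank-sum test at two-sided 0.05.

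*Under the null.* With five-category ratings and no difference, rejection was 0.040–0.053 for Fisher and 0.041–0.050 for Wilcoxon. Both hold their level.

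*Proportional-odds shifts, 15 per arm.* Ranges are over three assumed baseline distributions:

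| Odds ratio | Fisher | Wilcoxon |
|---|---|---|
| 3 | 0.184–0.225 | 0.318–0.374 |
| 5 | 0.363–0.413 | 0.600–0.637 |
| 8 | 0.578–0.660 | 0.816–0.846 |
| 12 | 0.748–0.806 | 0.929–0.936 |

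Two further simulations used an assumed control distribution of 10/25/35/20/10%. At odds ratios of 3, 5 and 8, one gave 17/40/64% for Fisher against 33/63/86% for Wilcoxon, and the other 20/44/63% against 38/66/84%.

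*Latent-normal shifts of d standard deviations* (cut-points −1.5, −0.5, 0.5, 1.5):

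| d | n per arm | Fisher | Wilcoxon | Relative loss |
|---|---|---|---|---|
| 0.75 | 12 | 0.169 | 0.351 | 1 − 0.169/0.351 = 52% |
| 0.75 | 15 | 0.237 | 0.452 | 48% |
| 1.0 | 12 | 0.310 | 0.573 | 46% |
| 1.0 | 15 | 0.419 | 0.688 | 39% |

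Across the proportional-odds and latent-shift grids the largest relative loss is this 52%. The smallest is at an odds ratio of 12 with 15 per arm: 1 − 0.806/0.932 = about 13%. The largest absolute gap is about 30 percentage points.

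**Adverse events: type I error.** If the two arms' event totals are compared by chi-square and the per-participant count has variance-to-mean ratio φ, the nominal 5% test rejects a true null with probability 2 × (1 − Φ(1.96/√φ)):

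- φ = 1: 0.050
- φ = 1.5: 1.96/1.225 = 1.600, giving 0.110
- φ = 2: 1.96/1.414 = 1.386, giving 0.166
- φ = 3: 1.96/1.732 = 1.132, giving 0.258

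Simulation with equal arms of 15 used Poisson events (independent) and gamma-Poisson events (clustered, shape k = 2, 1, 0.5, so φ = 1 + mean/k):

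| Assumed mean events per participant | Independent events | Clustered events | Fisher on participants with ≥1 event |
|---|---|---|---|
| 0.3 | 0.04–0.05 | 0.06–0.11 | 0.015–0.019 |
| 0.5 | 0.04–0.05 | 0.08–0.16 | 0.015–0.019 |
| 1.0 | about 0.05 | 0.11–0.25 | 0.015–0.019 |

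At a mean of 1.0, about 67% of simulated trials had more events than participants in at least one arm. A 2×2 table with events over participants could not then be formed.

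**The case against.** **The adverse-event phrase may be loose wording.** Section 2.8 assigns chi-square and Fisher's tests to categorical data reported as frequency and percentage, and a percentage suggests a participant denominator. Section 2.6.3 also collects occurrence, so a participant-level variable exists. The article condenses a fuller protocol, where the counting unit may be settled. This stands: under that reading the test is valid. But no passage of the article says so, and an analyst following the sentence as written would count events.

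**The size of the inflation is assumed.** The only adverse-event background, in the Discussion, reports three related cases from a review of nine trials and none in a trial of a modified comparator formula. It gives no usable rate. A reader might infer that the safety comparison has a false-positive rate well above 5%. The documents do not support that without conditions: the inflation needs the literal reading and clustering, and at low event rates it is modest.

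**Fisher's test on IMOS and IMPSS is valid.** This stands. A reader might infer that the test is wrong for the data or that half the power is lost. It keeps its error level, and half is the worst case under assumed ordered shifts. Section 2.8 also does not say whether the five categories are kept or collapsed to two, and the power comparison applies only if they are kept. At an odds ratio of 3 the better test still has only about 33–38% power with 15 per arm.

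**Materiality is modest.** The primary purpose is feasibility, the sample size makes no power claim, and IMOS and IMPSS are two of many secondary measures. This limits the weight of the point but is no reason to keep a less informative test when a better one costs nothing.

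**Conclusion.** The point holds in a limited form.

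- **IMOS and IMPSS:** a valid but inefficient choice. Kept in five categories, the ratings lose about 13–52% of the Wilcoxon test's power in relative terms, with 12 to 15 per arm. This rests on assumed proportional-odds or latent-normal shifts and assumed baseline distributions. The lack of a direction of effect does not depend on those assumptions.
- **Adverse events:** the sentence names the wrong unit. Read literally and with clustering, the type I error is about 6–11% at 0.3 events per participant and 11–25% at 1.0, where both the rates and the clustering are assumed. With independent events there is no inflation. If participants with an event were intended, this is a wording correction only.

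Both concern secondary or safety analyses. The feasibility outcomes and the primary effectiveness outcome, CSS at Week 6, are unaffected.

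**What to change.** Change two sentences in section 2.8, or settle them in the SAP, before unblinding:

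- Compare IMOS and IMPSS between arms by the Wilcoxon rank-sum test or a proportional-odds model, and tabulate the five categories by arm.
- State that the chi-square or Fisher's test compares the number of participants with at least one adverse event, and report event counts descriptively by arm.

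No new data, visits or participants are needed. The Wilcoxon rank-sum test is already named in the same section.

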### 2.5. Interventions

All investigational drugs were manufactured by Kyungbang New Pharmaceutical Co., Ltd. (Incheon, Republic of Korea) in compliance with the 2021 Korean Good Manufacturing Practice guidelines. All participants will be allocated to the *Maekmundong-tang* or *Saengmaek-san* groups. Each 2.5-g serving of *Maekmundong-tang* granule (Yunpye-tang extract granule, Maekmundong-tang; product code: 200005808) comprises grayish-brown granules that consist of 1250 mg *Maekmundong-tang* dry extract, 625 mg corn starch, and 625 mg lactose hydrate. The raw materials and composition of *Maekmundong-tang* dry extract 1250 mg are as follows: Liriopis seu Ophiopogonis Tuber 3.33 g, Pinelliae Tuber 1.67 g, Oryzae Semen 3.33 g, Zizyphi Fructus 1.00 g, Ginseng Radix 0.67 g, and Glycyrrhizae Radix et Rhizoma 0.67 g. Similarly, each 1.41 g serving of *Saengmaek-san* powder (Kyungbang *Saengmaek-san*, mixed single extract; product code: 200005617), the active control drug, is a brown powder that consists of 0.75 g Liriopis seu Ophiopogonis Tuber extract, 0.30 g Ginseng Radix extract, and 0.36 g Schisandrae Fructus extract. The investigator will instruct all participants to orally consume 1 pack of the formulation 3 times a day, before or between meals, for 6 weeks. Each of the herbal medicine was produced simultaneously in one batch and therefore has the same batch number. Their expiration date is 36 months from the date of manufacture. They should be stored in airtight containers at room temperature (1–30 °C). 

To improve the compliance of the participants of the clinical trial, the investigator will check the participant’s investigational product intake during the administration period and record details of compliance in the case report form (CRF); participants with less than 70% medication compliance at Week 6 will be dropped out.

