**ASSESSMENTS**						
CSS ***		●	●	●	●	●
Cough VAS		●	●	●	●	●
LCQ		●	●	●	●	
HARQ		●	●	●	●	
IMOS/IMPSS			●	●	●	
EQ-5D-5L/EQ-VAS		●	●	●	●	●
Yin Deficiency Questionnaire		●		●		
Cost questionnaire ****		●	●	●	●	●
Laboratory tests *****	●			●		
Adverse events investigation		●	●	●	●	
Compliance test			●	●		

* Including auscultation as well as nasal and throat examinations; ** Including X-ray examination of paranasal sinuses, if considered necessary by the investigator; *** Assessed by cough diary, except for the telephone survey conducted at Week 24; **** Questionnaire to record medical, non-medical (transportation, time, and nursing care), and productivity-loss costs due to chronic cough of participants; ***** Including hematological parameters, fasting blood glucose level, liver and renal function tests, electrolyte test, total IgE, and fibrinogen level. The urinary human chorionic gonadotropin level was assessed at the screening visit for only women of childbearing age. Abbreviations: CSS, Cough Symptom Score; ECG, electrocardiogram; EQ-VAS, the EuroQol Visual Analog Scale; EQ-5D-5L, a five-level version of the EuroQol Five-dimensional Descriptive System; HARQ, Hull Airway Reflux Questionnaire; IMOS, Integrative Medicine Outcome Scale; IMPSS, Integrative Medicine Patient Satisfaction Scale; LCQ, Leicester Cough Questionnaire; PICCQ, Pattern Identification for Chronic Cough Questionnaire; VAS, visual analog scale.

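### Electrolytes, fasting glucose and most haematology are drawn before and after treatment but have no named safety analysis, and the safety laboratory tests that are named get no between-arm comparison

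*Protocol article*

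**What the plan says.** The assessment schedule (Table 1) has one row for laboratory tests, marked at Visit 1 (screening) and Visit 4 (Week 6). Its footnote defines the panel as "Including hematological parameters, fasting blood glucose level, liver and renal function tests, electrolyte test, total IgE, and fibrinogen level".

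Section 2.6.3 (Safety Outcomes) is narrower (the quote breaks off before the week number, which is 6): "liver function (AST and ALT) and kidney function (blood urea nitrogen [BUN] and creatinine) tests will be conducted at the screening visit and at Week". It adds adverse events and vital signs: "the vital signs (blood pressure, pulse rate, and body temperature) will be measured at each visit and will be used as safety outcomes".

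Section 2.8 (Statistical Analysis) carries the same short list into the analysis: "AST, ALT, BUN, creatinine, and vital signs will be analyzed using a paired" t-test or Wilcoxon signed rank test, for the difference from before to after treatment. Between-arm testing of safety data is specified there only for the number of adverse events.

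Part of the panel is used elsewhere. Section 2.6.2 (Effectiveness Outcomes) states: "The serum biomarkers include eosinophils, total immunoglobulin E (IgE), and plasma fibrinogen, which will be evaluated at the screening visit and at Week 6".

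**The concern.** The article lists its laboratory safety variables twice, and both lists are shorter than the panel it schedules. A statistician who followed sections 2.6.3 and 2.8 as written would produce no safety table for electrolytes, glucose or most of haematology, although each participant who reaches Week 6 should have a value before and after treatment.

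The second problem is the form of the stated test. A before-after test of AST or creatinine mixes any effect of the product with time, regression to the mean and measurement drift. A change that is significant in one arm and not in the other is not evidence that the arms differ. The trial is randomised, and section 2.8 names no comparison that uses this for the safety laboratory values or vital signs.

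Safety is a stated aim in the Abstract and the Discussion, and the Discussion promises to evaluate the safety profiles of both products. Section 2.5 shows that their compositions differ. What is at stake is a safety summary that is silent on data already held. If extra tests were added after the data had been seen, the choice of variables could also be questioned.

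**Working it through.** **Step 1: tests drawn against tests named.** All groups below are drawn at screening and Week 6 (Table 1 and footnote).

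| Test group | Safety outcome (2.6.3) | Safety analysis (2.8) | Other named use |
|---|---|---|---|
| Liver and renal function | AST, ALT, BUN, creatinine | Same four, before-after | Eligibility (AST, ALT, creatinine; 2.3) |
| Electrolytes | No | No | None |
| Fasting glucose | No | No | None |
| Haematology | No | No | Eosinophils only, effectiveness (2.6.2) |
| Total IgE, fibrinogen | No | No | Effectiveness (2.6.2) |

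Of the three groups in question (electrolytes, glucose, haematology), 0 of 3 are in the safety outcomes and 0 of 3 in the safety analysis.

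**Step 2: could another purpose explain the draws?** The exclusion criteria in section 2.3 use AST, ALT and creatinine but set no electrolyte or glucose limit. A Week 6 sample cannot serve eligibility in any case. The article gives no other reason for repeating these tests after treatment.

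**Step 3: do the products differ?** Section 2.5 lists, per serving of Maekmundong-tang, Liriopis seu Ophiopogonis Tuber, Pinelliae Tuber, Oryzae Semen, Zizyphi Fructus, "Ginseng Radix 0.67 g, and Glycyrrhizae Radix et Rhizoma 0.67 g". Saengmaek-san consists of "0.75 g Liriopis seu Ophiopogonis Tuber extract, 0.30 g Ginseng Radix extract, and 0.36 g Schisandrae Fructus extract". Four of the six Maekmundong-tang components are not in the comparator, and Schisandrae Fructus is only in the comparator. This makes a between-arm safety contrast informative. It does not say which analyte would move.

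**Step 4: how much could the added analyses show?**

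- The plan's own figure (section 2.7): 24/(1 − 0.20) = 30 in total and 12/(1 − 0.20) = 15 per arm. Both are reproduced, so 12 to 15 per arm would have Week 6 values.
- Half-width of the 95% CI for a between-arm difference in mean change, in SDs of the change: t(0.975, 2n − 2) × √(2/n).
  - n = 12: 2.074 × √(2/12) = 2.074 × 0.408 = 0.85 SD.
  - n = 15: 2.048 × √(2/15) = 2.048 × 0.365 = 0.75 SD.
- Difference detectable at two-sided 0.05 with 80% power (the 80% is an assumption; the article states none), from the noncentral t distribution:
  - Paired test within one arm: 0.89 SD (n = 12), 0.78 SD (n = 15).
  - Between-arm t-test: 1.20 SD (n = 12), 1.06 SD (n = 15).

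Only large shifts would be detected by either test. Estimates with intervals, and counts crossing the reference range, are the useful output.

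**The case against.** The strongest reply is that this is a condensed article. The choice of analytes for the safety tables is ordinary analysis-plan content, and a schedule may list a broader panel than the text singles out. Neither section says that the four tests are the only ones. Three general statements also point towards wider coverage. The Abstract speaks of laboratory tests for safety without restriction. Section 2.8 includes all data from treated participants in the safety analysis. It also gives general rules for continuous data (independent t-test or rank sum test) and for intragroup change.

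Some of this stands. The full protocol may cover these tests, and that limits the severity. But the article is not silent: it itemises the laboratory safety variables in two places, and the lists agree with each other and not with its schedule. The sentence about all data defines the safety population and adds no variable. The general rules give methods without making electrolytes or glucose an outcome, and the specific safety sentence names a before-after test.

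Four stronger readings are tempting, and the documents do not support them:

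- **That a liquorice effect on potassium would be missed.** Glycyrrhizae Radix et Rhizoma is in one arm only, but the article says nothing about an electrolyte effect. Its Discussion reports rash and raised alkaline phosphatase as related to Maekmundong-tang. The mismatch does not need this rationale, and the article gives no incidence from which a number of missed cases could be calculated.
- **That the whole panel goes unused.** The four liver and renal tests, eosinophils, IgE and fibrinogen all have a named use.
- **That abnormal values would go unseen.** An investigator could record one as an adverse event, and adverse events are collected from Week 0 to Week 9 and compared between arms.
- **That blood pressure is overlooked.** It is already a safety outcome, measured at each hospital visit. What is missing is a named between-arm comparison.

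**Conclusion.** The point holds as a minor one. Electrolytes, fasting glucose and haematology other than eosinophils are collected before and after treatment without a named safety analysis. The safety laboratory tests and vital signs that are named get a before-after test and no stated comparison between arms. No stated figure changes, and the target of 30 is unaffected.

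The conclusion rests on reading sections 2.6.3 and 2.8 as the list of laboratory safety variables, which their matching wording supports. It needs no assumption about the pharmacology of either product. At 12 to 15 per arm the added results would describe and not test, and the trial's primary purpose, feasibility, is untouched.

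**What to change.** - In sections 2.6.3 and 2.8, add the electrolyte, fasting glucose and haematology results already in the Table 1 footnote to the safety outcomes and safety analysis.
- For all safety laboratory values and blood pressure, report the change from baseline (screening for the laboratory tests) to Week 6 by arm, with the between-arm difference and its 95% CI. Let this replace the before-after test as the main presentation.
- Add a normal/abnormal shift table by arm for the laboratory values and blood pressure.
- Say that these results are descriptive given 12 to 15 per arm, and settle the list before unblinding.

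The cost is a few more rows in the safety tables. No visit, sample or participant is added, and no dose or clinical rule changes.
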